**Figure 2 F2:**
[figure not shown]
Schedule of assessments Part B.

**Figure 3 F3:**
[figure not shown]
The surgical cavity simplified as a cube.

**Figure 4 F4:**
[figure not shown]
Overview of SPRAYDYE study activities.

### Outcome measures

#### Primary outcome

For both Part A and B, the primary outcome for the local and systemic safety and tolerability of a topical dose of AKRO-6qcICG is the occurrence of local and/or systemic treatment-emergent (serious) adverse events (TEA(S)AEs). AEs are defined as a medical occurrence in a subject to whom a medicinal product is administered. A serious adverse event (SAE) encompasses any undesirable medical incident experienced by a patient or trial participant, regardless of dosage, that leads to death, poses a threat to life, necessitates hospitalization, extends an ongoing hospital stay, causes enduring or substantial disability, or involves a significant medical event that, despite intervention, could have resulted in any of the aforementioned outcomes according to the investigator's professional judgement.

A treatment-emergent (serious) adverse event (TE(S)AE) is defined as an (serious) adverse event observed after starting administration of the specific treatment. If a patient experiences an event both prior to and after starting administration of a treatment, the event will be considered a TE(S)AE (of the treatment) only if it has worsened in severity (i.e., it is reported with a new start date) after starting administration of the specific treatment, and prior to the start of another treatment, if any.

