### Sample size

Six healthy volunteers and 16 breast cancer patients will be enrolled. As this is an exploratory study, the sample size is not based on formal statistical considerations. The proposed sample size will be sufficient to test the hypothesis.

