### Statistical analysis

Descriptive statistics will be depicted as mean (standard deviation, sd) or median (interquartile range, IQR). All statistical tests will be performed two-sided. A *p*-value of less than 0.05 will indicate a statistically significant difference. For part A and B, analysis of the safety and tolerability endpoints ((TE)(S)AEs, vital signs, ECG, and clinical laboratory tests) will be conducted with SAS 9.4 for Windows or newer (SAS Institute Inc., Cary, NC, USA). All (TE)(S)AEs will be listed and safety variable values outside the reference range will be flagged. Analysis of the pharmacokinetic endpoints (AUC_inf_, AUC_last_, CL/F, C_max_, t_1/2_, t_lag_, t_max_, Vz/F, Ae_last_, Ae_%_, CL/R) in plasma and urine will be conducted with R 3.6.1 for Windows or newer (R Foundation for Statistical Computing/R Development Core Team, Vienna, Austria, 2019). The individual PK parameters will be summarized per treatment group and, if applicable, will be presented graphically as boxplots. For Part B, the most recent version of SPSS (IBM, Armonk, New York, USA) will be used for statistical analysis of the exploratory NIR fluorescence imaging endpoints. Diagnostic accuracy analysis (including sensitivity, specificity, positive predictive value, and negative predictive value) will be performed based on a per resection wall (*in vivo* images)/per resection plane (*ex vivo* images) basis. To investigate differences in MFI between tumour tissue and adjacent healthy breast tissue on the surgical cavity walls and on the resection planes, the Wilcoxon signed-rank test will be used. The Spearman's correlation coefficient will be determined to investigate the correlation between the TBR of a fluorescent hotspot on a resection plane and the margin width at that location.

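### The last limb of the serious adverse event definition is worded the wrong way round, so an event kept from a listed outcome only by treatment may be labelled non-serious

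*Protocol article*

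**What the plan says.** In the protocol article, under Outcome measures, Primary outcome, the primary outcome for Parts A and B "is the occurrence of local and/or systemic treatment-emergent (serious) adverse events (TEA(S)AEs". The same section defines the terms on which this rests.

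- **Adverse event.** The definition is broad: "AEs are defined as a medical occurrence in a subject to whom a medicinal product is administered".
- **Serious adverse event.** Five outcomes come first, namely an event that "leads to death, poses a threat to life, necessitates hospitalization, extends an ongoing hospital stay, causes enduring or substantial disability". The last limb then adds an event that "involves a significant medical event that, despite intervention, could have resulted in any of the aforementioned outcomes", as judged by the investigator.
- **Treatment-emergent event.** It "is defined as an (serious) adverse event observed after starting administration of the specific treatment". This takes seriousness over from the SAE definition and does not restate the clause on intervention.

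Under Statistical analysis, the handling of these events is descriptive: "All (TE)(S)AEs will be listed and safety variable values outside the reference range will be flagged". The SAE definition appears nowhere else in the article, and no other section corrects it.

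**The concern.** The last limb serves events that were medically important but stopped short of the five listed outcomes. Often they stop short because someone treated them. The natural question is therefore what might have happened had nobody intervened. The printed clause asks the opposite: whether the outcome could have come about in spite of the intervention. On that wording, successful treatment counts against classifying the event as serious.

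At stake is consistent labelling of seriousness within the primary outcome of a first-in-human safety study. Part A volunteers are under observation for a treatment period of about 8 h, and Part B patients are dosed during surgery. In either setting an event can be treated on the spot without an admission or a longer stay, and its seriousness may then turn on this limb alone. Where the plain wording changes a label, it changes it from serious to non-serious.

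**Working it through.** No arithmetic applies. The point depends on no rate, effect size, error level or sample size, and the article states no figure to reproduce. The check is to apply the SAE definition limb by limb to four kinds of event after dosing, first as printed and then with the condition changed to *without intervention*.

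| Event | Limbs 1–5 (listed outcomes) | Last limb as printed, read plainly | Last limb with *without intervention* | Label changes? |
|---|---|---|---|---|
| (a) A listed outcome occurs | Met | Not needed | Not needed | No: serious both ways |
| (b) The event threatened life, or led to or prolonged a hospital stay, and was treated successfully | Met | Not needed | Not needed | No: serious both ways |
| (c) Treatment was given, a listed outcome stayed possible all the same, but none occurred | Not met | Met | Met | No: serious both ways |
| (d) Treatment was given and removed the danger; no listed outcome occurred, but one could have occurred untreated | Not met | Not met | Met | **Yes: non-serious as printed, serious if reworded** |

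Row (d) step by step:

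1. There is no death, threat to life, admission, longer stay or lasting disability, so the first five limbs fail.
2. The last limb asks whether one of these could have followed despite the treatment. By construction it could not, so this limb fails too.
3. The event is therefore not an SAE under the printed rule.
4. It still meets the broad adverse event definition, it arose after the start of administration, and it is listed. It stays in the primary outcome as a non-serious treatment-emergent event.

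Row (c) shows that the printed limb has some content. The words *could have* do not require that the event progressed, so the limb does not merely repeat the first five. Row (b) shows that much of what a safety reader would worry about is protected by the other limbs, whether or not treatment succeeded. The defect is confined to row (d).

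**The case against.** **The clause can be read another way.** It may be taken concessively: treatment was given, yet the event was of a kind that could have led to such an outcome. A treated and averted event would then qualify, and the reference to the investigator's judgement leaves room for this. The reading is possible but strained. If some investigators follow the words and others the evident intent, the same event gets different labels, which is itself a reason to correct the text.

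**The article condenses a protocol that is not shown.** The full protocol and the SAE form may be worded correctly. That limits any statement about how events will in fact be classified. It does not excuse the printed text, because this is a rule stated wrongly and not a detail left to another document.

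**The event is not lost.** This stands in full. Serious and non-serious treatment-emergent events both belong to the primary outcome and all are listed. Wound healing, pain, pruritus, vital signs, laboratory tests and ECG are also captured separately as secondary outcomes.

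Three stronger conclusions are tempting, and the article supports none of them.

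- *A reader might infer a numerical distortion.* One relabelled participant is 1/6 = 17 percentage points in Part A and 1/16 = 6 points in Part B. But these are one person over the group size and would fit any misclassification of any variable. The article sets no SAE proportion to be estimated, no SAE threshold and no test on SAE counts. On size it says: "As this is an exploratory study, the sample size is not based on formal statistical considerations".
- *A reader might infer that averted events are what this trial will mostly produce.* No rate of such events is given, and the section on expected limitations considers systemic exposure in Part B to be very low.
- *A reader might infer that the label decides whether Part B uses the 50 µM gel.* That step depends on the gel being well tolerated in Part A, but the article does not say how tolerability is judged or whether SAE labels enter into it.

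**Conclusion.** The clause is wrong as written. On its plain wording, an event kept from a listed outcome only by intervention, and meeting no other limb, may be labelled non-serious. The consequence is narrow: it touches only the serious or non-serious label, and only for that one group of events. Neither the count of treatment-emergent events nor the listing changes. No size of effect can be given from the article.

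The conclusion rests on two assumptions: that the clause is applied as its words read, and that the operative protocol and SAE form carry the same wording. If those documents are already correct, only the published sentence needs repair. The correction is still worth making, because the sentence is part of the definition of the primary outcome in a first-in-human safety study.

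**What to change.** Reword the last limb so that it covers a significant medical event that did not lead to one of the listed outcomes but, in the investigator's professional judgement, could have done so without intervention. Then confirm that the full protocol and the SAE form use that same wording.

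The cost is one clause and a check of two documents. Design, sample size, analysis and clinical management are unaffected. It should be done before the first participant is dosed, so that every event is classified under one rule; the article estimates the study start for Q3 2026.

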#### Secondary outcomes

For both Part A and B, secondary outcomes include wound healing, numeric rating scales of pain and pruritus at the site of administration, changes in vital signs (pulse, blood pressure, saturation and temperature), changes in clinical laboratory tests (haematology, blood chemistry, and urinalysis), changes in ECG parameters (heart rate, PR, QRS, QT, QTcF), and PK parameters.

#### Exploratory outcomes

In Part B, exploratory outcomes include the analysis of the NIR fluorescence images of the surgical cavity walls. Diagnostic accuracy of topically applied AKRO-6qc-ICG will be determined by categorizing each surgical cavity wall (*in vivo)* and resection plane (*ex vivo*) as true positive (fluorescent and tumour positive), true negative (not fluorescent and tumour negative), false positive (fluorescent and tumour negative) or false negative (not fluorescent and tumour positive). Additionally, the signal-to-background ratio (SBR) of fluorescent areas will be calculated.

### Training

For part B, prior to their first inclusion, surgeons and other involved hospital staff of the participating centre will be trained during a site initiation visit by the principal investigator or one of the coordinating investigators. The training will include the topical application of AKRO-6qICG and the use of the clinical fluorescence camera system to image the surgical cavity walls.

### Data collection

All outcome measures will be documented in case report forms (CRFs) by the coordinating investigator or trained local research staff. The clinical data will be prospectively registered via an electronic CRF (eCRF) in a digital database of Castor EDC. Additionally, the imaging data (visible light and NIR pictures of the cavity walls and resected specimen) will be collected for postoperative analysis.

### Data validation and management

Patient data will be registered coded. The research group from LUMC will have access to all coded data in the Castor EDC database. Core data leading to published results will be accessible in a technical appendix.

### Study timeline

The estimated study start is in Q3 2026. As only a limited number of subjects will be enrolled in Part A and B, data collection is expected to be finished within one year after study start.

### Statistical analysis

Descriptive statistics will be depicted as mean (standard deviation, sd) or median (interquartile range, IQR). All statistical tests will be performed two-sided. A *p*-value of less than 0.05 will indicate a statistically significant difference. For part A and B, analysis of the safety and tolerability endpoints ((TE)(S)AEs, vital signs, ECG, and clinical laboratory tests) will be conducted with SAS 9.4 for Windows or newer (SAS Institute Inc., Cary, NC, USA). All (TE)(S)AEs will be listed and safety variable values outside the reference range will be flagged. Analysis of the pharmacokinetic endpoints (AUC_inf_, AUC_last_, CL/F, C_max_, t_1/2_, t_lag_, t_max_, Vz/F, Ae_last_, Ae_%_, CL/R) in plasma and urine will be conducted with R 3.6.1 for Windows or newer (R Foundation for Statistical Computing/R Development Core Team, Vienna, Austria, 2019). The individual PK parameters will be summarized per treatment group and, if applicable, will be presented graphically as boxplots. For Part B, the most recent version of SPSS (IBM, Armonk, New York, USA) will be used for statistical analysis of the exploratory NIR fluorescence imaging endpoints. Diagnostic accuracy analysis (including sensitivity, specificity, positive predictive value, and negative predictive value) will be performed based on a per resection wall (*in vivo* images)/per resection plane (*ex vivo* images) basis. To investigate differences in MFI between tumour tissue and adjacent healthy breast tissue on the surgical cavity walls and on the resection planes, the Wilcoxon signed-rank test will be used. The Spearman's correlation coefficient will be determined to investigate the correlation between the TBR of a fluorescent hotspot on a resection plane and the margin width at that location.

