In Part B, 10 mL of 50 μM AKRO-6qcICG in thermosensitive gel (corresponding to 1.15 mg), if well tolerated in Part A, will be topically applied onto all surgical cavity walls of all patients (superior, inferior, medial, lateral, and posterior (Figure 2)) after the standard-of-care (SOC) BCS resection. After 10 min of incubation and three washing steps with cold saline, the surgical cavity walls will be imaged with an intraoperative, clinical, open-system, NIR fluorescence-sensitive camera. The assessments will be performed in a standardised sequence and will increase the duration of the surgical procedure by a total of 15 min. At sites of fluorescence signal, biopsies will be performed to correlate the fluorescence signal to the presence of residual tumour cells. After a biopsy is taken, the surgical cavity wall will be imaged again. Additionally, in parallel AKRO-6qcICG imaging gel will be topically applied *ex vivo* onto the SOC resection specimen. After 10 min incubation and three washing steps with saline, the resected specimen will be imaged with a NIR fluorescence-sensitive camera system to detect any tumour-positive resection planes. All NIR fluorescence images will be correlated to final histopathology. On the day of surgery, blood samples will be collected for PK analysis. The complete schedule of assessments are depicted in Figures 3, 4.

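### Accuracy per wall and plane, the signed-rank test and the hotspot correlation draw several units from each of 16 patients, with no allowance for within-patient correlation

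*Protocol article*

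**What the plan says.** The Sample size section of the protocol article states "Six healthy volunteers and 16 breast cancer patients will be enrolled" and adds "As this is an exploratory study, the sample size is not based on formal statistical considerations". Under Intervention, the gel goes "onto all surgical cavity walls of all patients (superior, inferior, medial, lateral, and posterior", so each patient supplies five walls; the resected specimen is treated and imaged in parallel.

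Under Exploratory outcomes, accuracy "will be determined by categorizing each surgical cavity wall" and each specimen plane as true or false, positive or negative. Statistical analysis then fixes the unit: "Diagnostic accuracy analysis (including sensitivity, specificity, positive predictive value, and negative predictive value) will be performed based on a per resection wall" in vivo, and per plane ex vivo. For fluorescence intensity (MFI) in tumour against adjacent healthy tissue, "on the surgical cavity walls and on the resection planes, the Wilcoxon signed-rank test will be used". Spearman's coefficient is to describe the "correlation between the TBR of a fluorescent hotspot on a resection plane and the margin width at that location". All tests are two-sided at 0.05.

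No section mentions within-patient correlation, a patient-level summary or a clustered variance. The limitations section warns that few or no walls may contain tumour, but does not mention dependence between walls.

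**The concern.** Walls of one patient share a tumour, a gel application, an incubation and wash, an imaging session and a tissue background. Their classifications and intensities are therefore likely to be positively correlated. The ordinary signed-rank test assumes independent pairs. A Spearman p-value, or a binomial interval on wall counts, assumes independent points.

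The Hypothesis section claims that the agent can detect residual cancer in the cavity, and these imaging analyses are the ones that bear on it. A specificity presented on 80 walls, or a p-value below 0.05 resting on a handful of patients, would make the proof of concept look firmer than 16 patients allow.

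**Working it through.** **Inputs from the article.** 16 patients (Sample size); 5 walls each (Intervention); two-sided 0.05 (Statistical analysis); a 10 to 40% positive-margin risk after breast-conserving surgery in general (Introduction). The plan gives no power, precision or interval to reproduce. The one count that follows from it is 16 × 5 = 80 walls.

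**Assumptions.** The ICC, the specificity (85%), the sensitivity (90%, used only to compare intervals under the fix) and the number of pairs or hotspots per patient. The article gives none of these.

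**1. Effective number of walls.** Design effect DE = 1 + (m − 1) × ICC with m = 5; effective walls = 80 / DE. The 95% half-width at 85%, if walls are independent, is 1.96 × √(0.85 × 0.15 / 80) = 0.078. It grows by √DE.

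| ICC | DE | Effective walls | Half-width | Simulated coverage, plain Wilson |
|---|---|---|---|---|
| 0.2 | 1.8 | 44 | 0.105 | about 88% |
| 0.3 | 2.2 | 36 | 0.116 | about 82–83% |
| 0.5 | 3.0 | 27 | 0.136 | about 76% |

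Coverage comes from beta-binomial simulation with 16 patients × 5 walls. Walls containing tumour drop out of the specificity denominator, so 80 is an upper bound.

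**2. Sensitivity.** At 10 to 40%, the expected number of tumour-positive patients is 16 × 0.10 = 1.6 to 16 × 0.40 = 6.4. With one positive wall per such patient, DE = 1. With two, DE = 1 + ICC, which is 1.1 to 1.5 at ICC 0.1 to 0.5. Clustering matters little here; the small number of positive walls matters more.

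**3. Signed-rank test.** A tumour-versus-healthy pair exists only where tumour is present, so the realistic case is a few patients with a few pairs each. Simulated type I error at nominal 5%, with normal patient effects:

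| Patients × pairs | ICC 0.3 | ICC 0.5 |
|---|---|---|
| 6 × 2 | about 7% | about 9% |
| 6 × 3 | about 12% | about 15–16% |
| 16 × 1 | about 4% | 4% |

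One pair per patient removes the problem.

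**4. Spearman.** Inflation needs both variables to cluster by patient. With 16 patients × 3 hotspots and the same ICC in both, type I error is about 7% at ICC 0.3 and 10% at 0.5. With 16 × 5 at ICC 0.1 it is 5.4%, which is negligible.

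**5. What a patient-level signed-rank test can show.** The smallest two-sided p is 2 / 2ⁿ: 0.0625 for n = 5 and 0.031 for n = 6. At least 6 tumour-positive patients are therefore needed. The binomial probability of 6 or more among 16 is 0.3% at a 10% rate and 67% at 40%. The article plans to enrol patients at high risk of positive margins, so the upper end, or beyond it, is the better guide.

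**The case against.** The strongest reply is that the article announces no confidence interval at all and, for Spearman, only that a coefficient will be determined. Per-wall sensitivity and specificity are legitimate descriptive figures, and interval methods are often left to a fuller document. This stands in part. A reader might infer that the plan prescribes binomial intervals and a Spearman p-value that ignore clustering. It does not, so those two parts of the point apply only if such figures are reported.

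The signed-rank unit is also implied rather than stated. The wording says where tissue is measured, and one pair per patient would be compatible with it. That too stands, as a condition on the type I error figures.

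A reader might infer a far larger inflation. Simulating five pairs from each of 16 patients gives about 17 to 25% at ICC 0.3 to 0.5, but on the cavity side that requires tumour on all 80 walls. The article's own expectation is far from that, since its limitations section allows that no patient may have residual tumour. Pairing tumour with adjacent healthy tissue also removes part of the shared camera, wash and background effect.

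Finally, the endpoints are exploratory, no success threshold is attached to them, and the primary safety outcome is untouched. This limits the weight of the point but does not remove it. The article does fix the wall and plane as the unit of accuracy, name the test and set a significance threshold, and nothing in it moves the analysis towards the patient.

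**Conclusion.** The point holds in a limited form. The stated unit of analysis ignores that several walls, planes or hotspots come from each of 16 patients. The main consequence is for specificity, where an unadjusted 95% interval would cover about 88 to 76% at ICC 0.2 to 0.5. A signed-rank test over several pairs per patient would run at about 7 to 16% in the realistic setting, and higher only if more patients and walls contain tumour. The Spearman effect is smaller, and sensitivity is barely affected.

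All of this rests on assumed positive ICCs and assumed numbers of units per patient. The per-wall point estimates are not wrong. The change should be made before the imaging data are analysed, but nothing in the primary outcome depends on it.

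**What to change.** - **Accuracy.** Keep the per-wall and per-plane estimates. Give each a 95% interval that accounts for clustering by patient and behaves with few patients and proportions near 100%. One example is a Wilson interval on the effective sample size from the patient-clustered variance, with the design effect held at 1 or above and a t quantile. In simulation this covers about 93 to 96% for specificity of 85%, and about 98 to 99% for sensitivity of 90% with 4 to 6 positive patients.
- **Avoid a percentile bootstrap by patient.** It covers only about 88 to 92% for specificity and about 44 to 65% for that sensitivity, because the interval often collapses to zero width when every positive wall is detected.
- **Signed-rank test.** State the unit. Use one tumour-minus-healthy MFI summary per patient, such as the median difference, separately for walls and planes. With fewer than 6 contributing patients, report descriptively.
- **Spearman.** Report the coefficient with a permutation by patient, or descriptively without a p-value.

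Cost: wider intervals, fewer units in the signed-rank test, and some calculation outside SPSS, which the article names for the imaging endpoints (SAS and R are named for safety and pharmacokinetics). No change to data collection or enrolment is needed.

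### The cavity test of tumour against adjacent healthy fluorescence is circular, because confirmed cavity tumour comes only from sites chosen for their signal; the specimen correlation describes hotspots only

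*Protocol article*

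**What the plan says.** All references are to the protocol article.

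- **Cavity sampling** (Intervention, Part B): "At sites of fluorescence signal, biopsies will be performed to correlate the fluorescence signal to the presence of residual tumour cells". No sampling of non-fluorescent cavity wall is described.
- **Intensity test** (Statistical analysis): "To investigate differences in MFI between tumour tissue and adjacent healthy breast tissue on the surgical cavity walls and on the resection planes", a Wilcoxon signed-rank test is to be used. The same section adds "All statistical tests will be performed two-sided" and takes a p-"value of less than 0.05 will indicate a statistically significant difference".
- **Correlation** (Statistical analysis): Spearman's coefficient is to describe the "correlation between the TBR of a fluorescent hotspot on a resection plane and the margin width at that location".
- **Ratio outcome** (Exploratory outcomes): "the signal-to-background ratio (SBR) of fluorescent areas will be calculated".
- **Mapping between specimen and cavity** (Introduction): because the excised tissue is soft, its shape no longer matches the cavity, and placing a positive specimen margin in the cavity can be very difficult.
- **Size** (Sample size): 16 patients in Part B, and "the sample size is not based on formal statistical considerations". Expected limitations and difficulties accepts that no patient may have residual tumour.

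**The concern.** A paired test of tumour against neighbouring tissue shows that an agent discriminates only if the tumour sites were chosen without regard to their brightness. In the cavity they are not. A site becomes known tumour by being biopsied, and it is biopsied because it fluoresced. The test then asks whether that site is brighter than the tissue beside it, which is close to the reason it was picked. Keeping only biopsies that prove positive does not undo this. If the agent had no specificity, positive and negative biopsies would be equally selected for brightness.

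Two things are at stake. A p-value below 0.05 could be read as support for the stated hypothesis that the agent can detect residual cancer in the cavity, when it may show only that fluorescent spots are brighter than their surroundings. And tumour that did not fluoresce, the failure that matters most for margin assessment, cannot enter the test.

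The specimen correlation has a related but milder limit. It is restricted to hotspots, so it is selected on one of its two variables, the tumour-to-background ratio (TBR). Close-margin sites without signal are left out.

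**Working it through.** The plan states no effect size, spread, brightness threshold or expected correlation, so there is no figure of its own to reproduce. The only inputs taken from the document are the two-sided 0.05 level, the signed-rank test and the fluorescence-driven biopsy rule. Everything else below is an assumption.

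**Step 1: can cavity tumour be located other than by a fluorescent biopsy?** The Intervention section says all images will be correlated with final histopathology. For the specimen this is independent of fluorescence. For the cavity, the Introduction says the specimen's geometry cannot be relied on to place tumour. The only site-level confirmation of cavity tumour described is therefore a biopsy at a fluorescent spot.

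**Step 2: the limiting case, exact.** If selection makes every biopsied site brighter than its neighbour, all n differences are positive. The exact two-sided signed-rank p-value is then 2/2^n. With n = 6 this is 2/64 = 0.031, below 0.05 whatever the histology.

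**Step 3: simulation with an agent of no specificity.** The log-MFI difference between site and neighbour is assumed normal with mean 0 and SD 0.5, so the true median ratio is 1.0. The test is the exact two-sided signed-rank test at 0.05.

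| How sites enter the test | n = 6 | n = 8 | n = 10 | n = 16 |
|---|---|---|---|---|
| No selection on fluorescence | about 0.03 | about 0.03 | 0.04–0.05 | 0.04–0.05 |
| Measured ratio above 1.01, 1.5 or 2.0 | 1.00 | 1.00 | 1.00 | 1.00 |
| Noisy visual call (threshold 1.5, call-noise SD 0.25 to 1.0) | 0.12–0.90 | 0.20–1.00 | 0.28–1.00 | 0.44–1.00 |

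Entries are rejection rates; the nominal rate is 0.05. With selection on the measured ratio, the apparent median ratio at n = 10 averages about 1.4, 1.9 and 2.4 for the three thresholds, although the truth is 1.0. The first can be checked by hand. Selecting ratios just above 1 leaves roughly a half-normal, whose median is 0.6745 × 0.5 = 0.337 on the log scale, and exp(0.337) = 1.40.

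**Step 4: effect of the hotspot restriction on Spearman's coefficient.** The result depends on the assumed shape.

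- *Bivariate normal, rho = -0.5:* the coefficient is -0.48 over all sites and -0.31 if only the top 50% of TBR values are kept. It weakens.
- *Log-TBR decaying exponentially with margin width to a flat background* (amplitude A, decay length L, hotspot cut-off 1.5):
  - Margins 0–10 mm, L = 5 mm, A = 0.7, noise SD 0.3: from -0.47 to -0.32. It weakens.
  - Margins 0–20 mm, L = 1 mm, A = 1.1, noise SD 0.3: from -0.21 to -0.46. It strengthens.

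The hotspot coefficient therefore need not equal the coefficient over all sites, and the direction of the difference cannot be settled from the document.

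**The case against.** The strongest reply is that these are exploratory analyses in 16 patients with a safety primary outcome, and that no decision is tied to the p-values. That stands and limits the weight of the point. It does not make the cavity test informative, because the plan still attaches a significance threshold to it.

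A second reply is that the article condenses a fuller protocol, which may set region-of-interest rules. The Exploratory outcomes section also provides for walls that are tumour-positive but not fluorescent, so some reference for such walls seems intended. This is fair. But classifying a whole wall does not show where on it to measure tumour MFI, and the biopsy rule as written is driven by fluorescence.

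Third, the numbers of pairs, the spread and the noise levels are not in the document. That also stands. The range at six pairs is wide, and 0.031 is a limiting case that takes every pair as brighter. What does not depend on those choices is the direction: every selected scenario tried rejected more often than 0.05, and the lowest rate was 0.12.

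A reader might infer three stronger claims, which the documents do not support:

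- *That the hotspot correlation is biased towards zero.* This follows from a bivariate normal model, and step 4 shows that it can reverse. The question of how brightness relates to margin width among hotspots is also legitimate and openly stated.
- *That the resection-plane Wilcoxon test is circular too.* Tumour there can be defined by histology, and nothing says those sites are chosen by fluorescence.
- *That the signal-to-background ratio is misreported.* It is openly defined for fluorescent areas. The caution is only that it should not be read as the contrast of tumour in general.

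**Conclusion.** The concern holds for the cavity-wall Wilcoxon test. As the sampling is described, a significant result would not show that the agent separates tumour from healthy tissue, because selection alone can produce it: p = 0.031 with six uniformly brighter pairs, and a false-positive rate of about 0.12 to 0.90 at six pairs under the assumed noisy visual call, against about 0.03 without selection. This rests on the biopsy rule being complete as printed and on specimen pathology not locating tumour in the cavity, as the Introduction indicates. The simulated rates also rest on the assumed spread and call noise.

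The hotspot correlation is a limit of scope, not a demonstrated bias: it answers a question about hotspots only. The point deserves correction before the images are analysed, but it is of moderate weight because it concerns exploratory endpoints.

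**What to change.** **Cavity.** Remove the p-value for tumour against adjacent tissue. Compare background-normalised MFI between tumour-positive and tumour-negative biopsies instead, allowing for several sites per patient. Both groups are selected for fluorescence, so an agent without specificity would no longer produce a difference through that selection. If positives are too few, which the article itself foresees, report the values descriptively. Give the signal-to-background ratio separately by biopsy result. State plainly that neither analysis addresses tumour that did not fluoresce.

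**Specimen.** Keep the hotspot correlation, labelled as describing hotspots only. Where histology and images can be matched, add a correlation that includes close-margin sites chosen by histology, measured whether or not they fluoresce. For the resection-plane Wilcoxon test, a sentence saying that tumour sites are defined by histology would be a useful safeguard.

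**Cost.** Plan wording and some extra image measurement; the cavity part uses biopsies and images already planned and needs no further tissue. The added specimen analysis depends on histology being matched to the images, which the article does not promise at site level. The reported contrast will probably be less favourable.
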